# A randomised waitlist-controlled trial protocol for examining the efficacy of a nature-based intervention (angling) for military veterans and emergency service personnel with post-traumatic stress disorder (PTSD)

**DOI:** 10.1186/s13063-026-09506-9

**Published:** 2026-02-13

**Keywords:** PTSD, Nature-based social prescribing, Nature-based interventions, Veterans, Depression, Anxiety, Wellbeing, Angling, Fishing, Peer support, Green exercise, Ecotherapy, Veteran, Police, Fire service, Ambulance, Coast guard, ESP, NBI, Emergency service personnel

## Abstract

**Background:**

Post-traumatic stress disorder (PTSD) is a severely debilitating psychological condition that can affect one’s capacity to work and well-being. Nature-based interventions (NBI) offer a unique avenue for treatment without the typical barriers current psychotherapeutic treatments create for veterans and emergency service personnel (ESP). Data from a pilot study involving military veterans suggests angling as one such NBI, but large-scale robust experimental work is required to assess the causal impact of NBIs. We will therefore conduct a full-scale randomised controlled trial powered to provide definitive evidence of the efficacy of a nature-based, group angling intervention for military veterans and emergency service personnel with PTSD.

**Methods:**

We will recruit 264 participants for a randomised waitlist-controlled trial of a 2-day, 1-night nature-based angling intervention. We will compare PTSD, anxiety, depression, and wellbeing outcomes between an active and control group. The primary outcome relates to the comparison of pre-intervention (2 weeks before the intervention), with post-intervention measures for the active and control groups taken at 2 and 4 weeks after the intervention. We will also assess if the changes in PTSD scores in the active group might be considered clinically significant and reliable by comparing baseline (2-week pre-intervention) and 2-week and 4-week post-intervention PTSD scores. Secondary outcomes include examining loneliness, expressed anger using baseline and 4-week post-intervention scores. Long-term efficacy will be assessed by 6- and 12-month follow-up surveys. Cost-effectiveness will also be assessed. Process analyses will include examining the contribution of mood change, nature restoration, peer support, and skill learning experiences to the outcomes during the intervention scores at the beginning and end of the intervention.

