### Objectives {7}

Primary outcome objectivesAssess mean changes in mental health outcome measures (e.g. PTSD, see item “Outcomes {12}” for a full list) from pre- to post-intervention between active and control groups (see item “Statistical methods for primary and secondary outcomes {20a}” for analysis details).Secondary outcome objectivesAssess proportion of participants achieving clinically significant change and reliable change between 2-week pre- and 4-week post-intervention PTSD scores.Conduct sub-group analyses to evaluate mean change in primary outcomes by stratification factors (military veteran vs. ESP, PTSD severity, gender).Assess mean change in social loneliness, work and social adjustment, and anger expression from pre- to post-intervention between active and control groups.Assess mean change in primary outcome measures from baseline to 6 months and 12 months for the active intervention group only.Assess mean change in process measures (e.g. mood, see item “Outcomes {12}” for a full list) and physiological data (heart rate variability and eye movement) from day 1 to day 2 of the NBI experience.Assess the relationship between intervention experiences and changes in process measures from day 1 to day 2 of the intervention and their relationship to change in outcomes.We will also explore the cost-effectiveness and social return of investment of the intervention.

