### Outcomes {12}

#### Primary outcome measures

The following measures will be employed to evaluate the effectiveness of the intervention and will be assessed 2 weeks before the intervention and 2-week and 4-week post-intervention. The National Institute for Health and Care Excellence (NICE) [8], recommends the use of self-report measures for evaluation of outcome in PTSD interventions. These measures of PTSD, anxiety, depression, and wellbeing were used in the development phase, establishing their acceptability and sensitivity to change over the short to medium term: PTSD symptoms are assessed by the PTSD Checklist for DSM-5 (PCL-5) [9], Depression by the Patient Health Questionnaire-9 (PHQ-9) [10], and Anxiety by the General Anxiety Disorder-7 Scale (GAD-7) [11]. Participants will also complete the 7-item Short Warwick-Edinburgh Mental Wellbeing Scale (WEMWBS) [12] to evaluate positive feelings of wellbeing. Mean change from baseline will be assessed for each of these outcomes for active intervention and control groups.

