#### Secondary outcome measures

Use subheadings (or just numbers that correspond to the objectives) under this heading following the same order as in the introduction statement of objectives:Using scores on the PCL-5 [9], we will assess the proportion of participants achieving clinically significant change and reliable change between 2-week pre- and 4-week post-intervention in the following ways: clinically significant change equates to a decrease in PTSD score of greater than or equal to 10, and reliable change reflects a decrease in PTSD score of greater than or equal to 5.Sub-group analyses will be carried out to evaluate mean change in the primary outcome measures (described above) by stratification factors (military veterans vs emergency service personnel), PTSD severity (high vs low), and gender (male vs female).The following measures of loneliness and expressed anger were included in the developmental phase and will be assessed as follows: Loneliness will be assessed by the Short Version of the Social and Emotional Loneliness Scale for Adults (SELSA-S) [13]: 2 weeks prior and 2- and 4-week post-intervention. Expressed anger will be assessed by the State–Trait Anger Expression Inventory (STAXI) [14], which measures how frequently participants have expressed anger verbally or physically in the last month. This will be taken 2-week pre-intervention and 4-week post-intervention. The Work and Social Adjustment Scale (WSAS) [15] is a 5-item measure of impairment in general social functioning. This will be measured 2-week pre-intervention and at a 6-month and 12-month follow-up since it will not be sensitive to short-term change. Mean change from baseline will be assessed for each of these outcomes for active intervention and control groups.Follow-up measures at 6 and 12 months: It is not possible to include long-term follow-up measures in the RCT because the waitlist group will receive the intervention after the RCT 4-week data collection is completed. Instead, we will take measures of PTSD symptoms, anxiety, depression, wellbeing, loneliness, expressed anger, and social functioning, to provide pre- and post-data from the intervention fishing group only at 6 months and 12 months after their intervention. We will also measure changes in NHS (National Health Service) service use and employment at these times. In addition, to gauge the impact of the NBI on long-term behaviour and engagement with nature-based activities, we will follow-up on the participant exit strategy to assess how participants have engaged with angling or other nature-based activities since the intervention. Mean change from baseline to follow-up will be assessed.Mean changes in process measures (mood and physiological changes) will be assessed between the beginning of day 1 of the intervention to the end of day 2. We will evaluate mood using the brief Profile of Mood States (POMS) [16]. Our developmental phase has shown that these measures are sensitive to detect change between arrival and departure at the intervention. Following consultation in the development phase, we include objective physiological measures of psychological states: pulse heart rate and heart rate variability and assess hypervigilance using a mobile eye-tracking device to quantify saccadic behaviour.*Measures of the hypothesised active elements of the intervention*: We developed an item pool during the developmental phase. These measures will be taken prior to departure. Eight items from the Perceived Restorativeness Scale (PRS) [17] measure perceived experience of restoration from the environmental surroundings. Bespoke questions have been developed to evaluate self-efficacy, experience of fishing, and being in a group of veterans. Fourteen questions explore participants’ experience of fishing (e.g. “I found I could focus on the fishing”). Eleven questions explored participants’ experience of peer support over the weekend (e.g. “I felt the people around me understood”). These questions are answered by participants at the end of day 2 of the intervention. We will assess the relationship between intervention experiences and changes in process measures and any potential interaction with outcome measures over the course of the trial.The cost-effectiveness and social return of investment will be analysed based on the Greater Manchester Cost-Benefit Analysis Model [18]. This will allow for comparisons to be made with other treatments and studies using government-approved values.

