#### Secondary analyses

We will assess if the changes in PTSD symptoms observed might be considered clinically significant or reliable. We will assess clinically significant change (a decrease of > = 10 points on the PCL-5) and reliable change (as decrease of > = 5 points on the PCL-5) between the baseline and 2-week and 4-week post-intervention. All analyses will be carried out on veterans and emergency service personnel combined.Subgroup analysis of primary outcomes by stratification factors will be conducted using mixed MANOVA (intervention vs waitlist) × repeated measures on all outcomes (baseline vs 4-week post-intervention) separately for each stratification factor.A mixed MANOVA with one between-group factor (intervention vs waitlist control) and repeated measures on secondary outcomes (loneliness, expressed anger, work and social adjustment)Within-participant analyses will be used to assess change from baseline to 6 months and 12 months for the intervention group only.A psychometric analysis of process measures will be conducted via factor analysis and reliability analysis. Path analyses will explore the relationship of process measures regarding the intervention experience to mood change assessed via the POMS questionnaire and psychophysiological data during the intervention and change in outcomes.See item e. above.A cost-benefit analysis will be used to analyse the cost of effectiveness and social return of investment of intervention based on the Greater Manchester Cost-Benefit Analysis model, which allows for comparisons with other treatment/projects based on government-approved values.

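### Clinically significant and reliable PCL-5 change has no stated comparison with the waitlist, the 5-point reliable label has no support in the protocol, and the time points conflict

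*Protocol article*

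**What the plan says.** Four places in the protocol article deal with this endpoint.

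- **Abstract, Methods:** "We will also assess if the changes in PTSD scores in the active group might be considered clinically significant and reliable", comparing baseline with both 2 and 4 weeks after the intervention. This is the only place that says which arm is meant.
- **Objectives {7}:** the proportion of participants who meet each criterion, "between 2-week pre- and 4-week post-intervention PTSD scores". No arm and no contrast is named.
- **Outcomes {12}, Secondary outcome measures:** "clinically significant change equates to a decrease in PTSD score of greater than or equal to 10". The time point here is again 4 weeks only. For the lower cut-off the section's wording is: "reliable change reflects a decrease in PTSD score of greater than or equal to 5".
- **Statistical methods {20a}, Secondary analyses:** "We will assess if the changes in PTSD symptoms observed might be considered clinically significant or reliable". The 5-point criterion is repeated as "reliable change (as decrease of > = 5 points on the PCL-5"), assessed at 2 and 4 weeks. No control proportion, test or effect measure is given.

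Two nearby sentences do not fill the gap. In Secondary analyses, "All analyses will be carried out on veterans and emergency service personnel combined" pools the two service groups, not the trial arms. In Secondary outcome measures, the sentence about active and control groups follows loneliness, anger and work and social adjustment, and concerns mean change in those scales.

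On the instrument, the Primary outcome measures section says "PTSD symptoms are assessed by the PTSD Checklist for DSM-5 (PCL-5") and gives no SD, reliability or confidence level from which a reliable-change limit could be obtained.

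**The concern.** The trial randomises a waitlist and collects PCL-5 scores in it at baseline, 2 weeks and 4 weeks for the primary comparison. Judging individual change in the active arm alone sets that comparator aside for the one endpoint that speaks most directly to clinical impact. Some people will cross a 5- or 10-point threshold through measurement error or untreated change, and without the waitlist proportion the reader cannot tell how many.

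The word reliable adds to this. In its usual sense, reliable change is change too large to be put down to measurement error, so whether 5 points qualifies depends on the SD and reliability of the scale. The protocol fixes the cut-off without either.

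Finally, with 4 weeks in two sections and 2 and 4 weeks in two others, the time point for the headline proportion is open to choice after the data are seen.

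**Working it through.** **The plan's own figure.** Sample size {14} gives d = −0.52, two-sided alpha 0.05, 95% power and 98 per arm. The normal approximation gives n = 2(1.960 + 1.645)² / 0.52² = 96.1, so 97 per arm. Exact t-test power is 0.9498 at 97 and 0.9517 at 98. The planned 196 is reproduced, and 98 per arm is used below.

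**Inputs.** Cut-offs of 5 and 10 points come from Outcomes {12}. PCL-5 SD and reliability r are not in the document. They are assumed here as SD 12 to 18 and r 0.95 to 0.85.

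**Formulas.** The SD of the difference between two measurements due to error alone is S = SD × √(2(1 − r)). The 95% reliable-change limit is 1.96 × S. With no true change, the share falling by c points or more is Φ(−c/S).

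| SD | r | S | 95% limit | Fall ≥ 5 | Fall ≥ 10 |
|---|---|---|---|---|---|
| 12 | 0.95 | 3.79 | 7.4 | 9.4% | 0.4% |
| 15 | 0.90 | 6.71 | 13.1 | 22.8% | 6.8% |
| 18 | 0.85 | 9.86 | 19.3 | 30.6% | 15.5% |

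First row as an example: S = 12 × √0.10 = 3.79; 1.96 × 3.79 = 7.4; Φ(−5/3.79) = 0.094; Φ(−10/3.79) = 0.004.

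**Reliability needed for 5 points to be the 95% limit.** r = 1 − (5 / (1.96 × SD))² / 2, which is 0.977 at SD 12, 0.986 at SD 15 and 0.990 at SD 18.

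**Wider range.** Over SD 10 to 20 and r 0.80 to 0.95, the 95% limit runs from 6.2 to 24.8 points. It is above 5 in every combination tried.

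**Is a between-arm comparison feasible?** Assume a uniform shift of 0.52 × SD in the active arm, no true change in controls, SD 12 to 18 and r 0.80 to 0.90. Then p(control) = Φ(−c/S) and p(active) = Φ((0.52 × SD − c)/S).

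- Fall of 5 or more: about 18 to 33% in controls against 57 to 71% in the active arm; power above 0.99 with 98 per arm.
- Fall of 10 or more: about 3 to 19% against 24 to 48%; power about 0.97 or more.

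The uniform shift is a simplification, so this shows only that the comparison is practicable at the planned size.

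**Time points side by side.** Objectives {7} and Secondary outcome measures: 4 weeks. Abstract and Secondary analyses: 2 and 4 weeks.

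**The case against.** The restriction to the active group is one phrase in the abstract. The body of the protocol speaks of participants and does not exclude the waitlist. Methods {20c} promises a detailed statistical analysis plan, which could add the comparison. Efficacy rests on a randomised comparison of means, and this endpoint is secondary. All of that stands, and it limits how serious the point is. It does not remove it: the only text that names an arm names the active one, and the same sections write out between-arm contrasts for the primary outcomes and for loneliness, anger and work and social adjustment.

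The reliable-change limit also rests on assumed inputs, including the 95% level. That stands too. A 90% limit would still be 1.645 × 3.79 = 6.2 to 1.645 × 9.86 = 16.2 points. But a source for the 5-point cut-off may exist that the article does not show, so the supportable statement is that the document gives no basis for the label, not that 5 points can never be reliable.

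Some stronger readings are tempting and are not supported:

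- **Regression to the mean will be counted as benefit.** It is plausible with self-referral but cannot be quantified. Eligibility {10} states no PCL-5 threshold. PCL-5 items are taken at registration, apart from the measurement 2 weeks before the intervention, so some regression may occur before the change score starts. Sample size {14} reports significant improvement in the developmental phase for the angling group but not the controls; that does not prove zero change, but it gives no support for a large untreated fall.
- **Higher false-positive rates.** An SD of change of 8 to 12 points would give 27 to 34% and 11 to 20%. That does not match the reliability assumptions above, which imply S of 3.8 to 9.9, and a wider spread would include real individual change.
- **Worsening goes unreported.** Increases enter the between-arm mean change, and item {22} covers psychological distress and flashbacks as potential adverse events, with written records of non-serious events.

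**Conclusion.** The point holds as a moderate one about a secondary endpoint. As written, clinically significant and reliable change is confined to the active arm in the abstract and has no stated control comparison elsewhere. With no true change, measurement error alone would put about 9 to 31% of participants over the 5-point criterion and 0.4 to 15.5% over the 10-point criterion, so a single-arm proportion is not interpretable as benefit. The 95% reliable-change limit is 7.4 to 19.3 points on the same assumptions, and the protocol offers nothing to support calling 5 points reliable. These figures depend on SD 12 to 18, reliability 0.95 to 0.85 and normally distributed error, none of which the document states. The conflict over time points and the missing contrast do not depend on any assumption. A reader should not infer that the trial's efficacy claim is compromised: the primary comparison of means is between arms and is unaffected.

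**What to change.** Align the abstract, Objectives {7}, Secondary outcome measures and Secondary analyses as follows.

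1. Report the proportions with a decrease of at least 5 and at least 10 points in both randomised arms.
2. Compare the arms at 4 weeks by a risk difference with 95% CI, adjusted for baseline PCL-5 (the measurement from which change is counted) and the minimisation factors. Present 2 weeks as supportive.
3. Keep the pre-specified 5- and 10-point cut-offs; a threshold derived from the trial sample would give up that pre-specification. Describe the first as a decrease of at least 5 points, and use the word reliable only if a stated SD, reliability and confidence level support it.
4. Optionally, tabulate increases of the same size by arm.

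The cost is a few extra tables and some rewording; the data are already being collected. The downside is a less favourable label for small improvements. Recruitment runs to September 2026 and the analysis plan is to be agreed before data entry ends, so the change can still be made prospectively.

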### Trial design {8}

A randomised waitlist-controlled superiority trial with an allocation ratio of 1:1 and a 4-week follow-up. The primary outcome will be assessed at 2-week and 4-week post-intervention and compared with the waitlist control group. The total follow-up period is 12 months (intervention group only).

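### The abstract promises long-term efficacy, but the 6- and 12-month data are uncontrolled change in the intervention arm and cannot show it

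*Protocol article*

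**What the plan says.** The abstract's Methods paragraph presents the later surveys as a test of efficacy: "Long-term efficacy will be assessed by 6- and 12-month follow-up surveys".

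The body of the protocol describes something narrower:

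- Objectives {7}, among the secondary objectives: "Assess mean change in primary outcome measures from baseline to 6 months and 12 months for the active intervention group only".
- Trial design {8}: a superiority trial with a 4-week follow-up, and a total follow-up of 12 months that applies to the intervention group alone.
- Secondary outcome measures, giving the reason: "It is not possible to include long-term follow-up measures in the RCT because the waitlist group will receive the intervention"; this happens once the 4-week data are in.
- Secondary analyses: "Within-participant analyses will be used to assess change from baseline to 6 months and 12 months for the intervention group only".

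The same follow-up also collects economic quantities: "We will also measure changes in NHS (National Health Service) service use and employment at these times". As a separate item, "The cost-effectiveness and social return of investment will be analysed based on the Greater Manchester Cost-Benefit Analysis Model". The article does not say which data feed that model or over what horizon.

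**The concern.** Efficacy is a causal claim: the outcome compared with what would have happened without the intervention. In this trial the waitlist arm supplies that comparison at 2 and 4 weeks, and no one supplies it afterwards. At 6 and 12 months the only estimate is the intervention arm against its own baseline.

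Several other processes can move that estimate:

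- the natural course of symptoms over a year;
- usual care, which continues with nothing prohibited (Relevant concomitant care {11d});
- selective follow-up, since attrition after randomisation was already about 25% in the development phase (Recruitment sample size);
- regression to the mean, if people tend to enter when symptoms are worse than usual for them.

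The trial is commissioned to supply experimental evidence of causal impact for policy. A reader of the abstract sees long-term efficacy beside the words for a randomised controlled trial and is not told that the randomised comparison stops at 4 weeks.

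**Working it through.** **1. The plan's own figure.** The sample size rests on the between-group difference at 4 weeks: d = 0.52, two-sided alpha 0.05, 95% power (Power analysis). A two-sample t-test needs 97.1 per arm, so 98 per arm and 196 in total, with power 95.2%. The stated figure reproduces. It covers only the randomised 4-week contrast; no figure is given for 6 or 12 months.

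**2. How small a within-arm change reaches significance.** Input: 132 randomised to the intervention (Recruitment sample size). Assumption: the 25% attrition seen in development also applies here, so n = 132 × 0.75 = 99. A paired t-test is significant when the mean change exceeds t(0.975; 98)/√99 = 1.984/9.950 = 0.20 SD of the change score. With an assumed baseline to follow-up correlation r = 0.7, the change-score SD is √(2(1 − 0.7)) = 0.775 baseline SD, so the threshold is 0.199 × 0.775 = 0.15 baseline SD. That is under a third of the planned 0.52.

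**3. What zero effect can produce.** The protocol gives no PCL-5 entry threshold, SD or correlation, so everything in this step is assumed. A paired test is used only as an illustration; the protocol does not name one. All results are for n = 99.

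*Selection acts on the baseline score.* Suppose the lowest fraction q of the source population does not enter. With c the normal quantile of q, λ = φ(c)/(1 − q) and δ = λ(λ − c):

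- expected drop = (1 − r)λ
- variance of change = 2(1 − r) − (1 − r)²δ

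Example, r = 0.6 and q = 0.5: λ = 0.798, δ = 0.637; drop = 0.4 × 0.798 = 0.319 SD; SD of change = √(0.8 − 0.16 × 0.637) = 0.836; standardised change = 0.319/0.836 = 0.382; chance of p < 0.05 = 96%.

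| r | q = 0.10 | q = 0.25 | q = 0.50 |
|---|---|---|---|
| 0.6 | 14% | 50% | 96% |
| 0.7 | 12% | 39% | 89% |
| 0.8 | 10% | 27% | 73% |
| 0.9 | 7% | 16% | 43% |

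*Selection acts on the registration score and baseline is re-measured.* This is closer to the protocol: PCL-5 items are taken at registration (Recruitment {15}) and the outcome baseline 2 weeks before the intervention (Primary outcome measures). The expected drop becomes (r1 − r2)λ, with r1 the registration–baseline and r2 the registration–follow-up correlation. The variance of change is 2 − 2·r3 − (r1 − r2)²δ, with r3 the baseline–follow-up correlation.

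- r1 = r2 = r3 = 0.8: drop 0, chance 5%.
- r1 = 0.85, r2 = 0.65, r3 = 0.7, q = 0.5: drop 0.2 × 0.798 = 0.160 SD; SD of change 0.758; standardised change 0.211; chance 55%.

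*Any non-specific improvement of m baseline SD, whatever its cause.* Standardised change = m/√(2(1 − r)), for r = 0.6 to 0.8:

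- m = 0.1: 20% to 34%
- m = 0.2: 60% to 88%
- m = 0.3: 91% to 99.7%

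**4. The economic items.** Health service use is collected at recruitment (Plans for assessment and collection of outcomes {18a}). The only later service-use and employment measurement described is the one at 6 and 12 months, in the intervention arm. No later control-arm measure is described.

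**The case against.** The strongest reply is that the protocol hides nothing. Every body section that mentions the later follow-up says it is intervention group only, the reason is given openly, long-term change is a secondary objective, and the efficacy wording sits in one abstract sentence. Loss of the control after crossover is inherent in a waitlist design, whose choice the protocol justifies. All of this stands, and it makes the fault one of labelling. It does not remove the fault: explaining why a control is absent is not the same as limiting the inference, and no section does the latter.

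Four stronger readings are tempting, and the documents do not support them.

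- *That the plan tests the change against zero.* It says only that within-participant analyses will assess change. A test is plausible, but none is named, and detail is deferred to a statistical analysis plan.
- *That it makes an uncontrolled savings claim.* No such claim appears, and the inputs to the cost-benefit model are not stated. The point is conditional on the later data being used there.
- *That participants enter at a peak of distress, so regression to the mean is certain.* The protocol permits self-referral and also uses referring agencies. It states no PCL-5 threshold, and baseline is a separate assessment, so some regression may already have occurred by then.
- *That a spurious significant result is likely.* A high false-positive figure requires assuming a sizeable elevation at entry. Mild selection, or a re-measured baseline with stable correlations, brings the rate back near the nominal 5%.

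**Conclusion.** The point holds as a mismatch between claim and design. The abstract announces long-term efficacy; the planned estimate is uncontrolled change in one arm. That follows from the text and needs no assumption.

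The size of the possible bias cannot be fixed from the documents. The range of about 5% to over 95% for a significant change with no intervention effect depends on assumed selection, correlation and retention, and no single value in it should be quoted as the expected rate. It shows only that a significant within-arm change would be weak evidence of a lasting effect. Natural course, usual care and selective follow-up would remain even if regression to the mean were nil.

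The randomised 2- and 4-week comparison and its sample size are unaffected. The consequence is confined to what may be concluded beyond 4 weeks.

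**What to change.** - In the abstract, replace the long-term efficacy wording with *uncontrolled change in the intervention arm at 6 and 12 months*.
- In Secondary analyses and in the statistical analysis plan, report these results as estimates with confidence intervals, described as uncontrolled.
- State that conclusions about efficacy rest on the randomised 2- and 4-week contrast only.
- If the 6- and 12-month NHS-use or employment changes enter the cost-benefit or social-return analysis, label those results as an uncontrolled scenario.

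The cost is wording in the protocol and analysis plan. No new data, visits or participants are needed. The downside is a more modest long-term claim.
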